### Secondary outcome analysis will include

Comparison of the proportion of patients in each group who achieved good actual adherence (defined for this study as ≥80 %) as well as the number progressing to good technique (≥80 % of all doses attempted by the patient classified as correct technique) at both 2 and 6 months will be assessed. Changes in patterns of adherence in the intervention and comparator groups will also be reviewed by looking at the morning and evening habit of inhaler use, error rates, overdose rates, intervals and attempted rates of adherence.

The PEFRs, SGRQ responses and rescue medication (inhaler, steroid, antibiotic) use of the intervention and comparator groups will be compared, as will levels of reported symptoms (as noted in the participants’ respiratory diaries) and improvement in participants’ ‘breathing-related goals’.

Prescription medication dispensing records will be reviewed to provide a further assessment of adherence (as defined by the medication possession rates and/or the proportion of days covered method) pre, during and post the study, and adherence measured in this way will be compared across the intervention and comparator groups; it will also be compared with actual adherence rates determined by the INCA® device.

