## Background

Asthma and chronic obstructive pulmonary disease (COPD) are common, chronic respiratory diseases [1, 2]. Both conditions are characterised by symptoms such as wheeze, breathlessness and airflow limitation [3, 4] which vary in intensity from patient to patient.

Appropriate pharmacological treatment, used correctly, can help to reduce symptoms and improve quality of life [3, 4]. Inhaled medications are commonly prescribed but can be difficult to use and this can lead to technique errors [5, 6] that may have both direct costs such as medication waste, and indirect costs such as increased use of other health care resources as a consequence of poor symptom control [7].

Community pharmacist-delivered interventions have been shown to improve inhaler technique [8, 9], inhaled mediation adherence rates [10] and therapeutic outcomes [11–14] for adult patients with asthma [8, 9, 11–14] and COPD [8, 10]. However, adherence rates in reported studies are frequently either based on patient self-report which has been shown to be unreliable [15, 16] or calculated from pharmacy databases containing prescription refill data which provide information on medication obtained but not on how such medication is used in practice [17, 18].

We developed a device, INCA®(INhaler Compliance Assessment), which makes a digital acoustic recording of an inhaler being used [19]. In this study the device is attached to a salmeterol/fluticasone Diskus® (Seretide Diskus®, also known as Seretide Accuhaler®) inhaler. When a patient opens their Diskus® inhaler (by sliding a thumbgrip to expose the mouthpiece) the INCA® device switches on and begins to audio record. The recordings are analysed using automated signal processing techniques, thus providing an objective assessment of both time and technique of inhaler use [19].

Participants’ adherence to their inhaled medication will be described in terms of both attempted and actual adherence rates. Where the participant opens their Diskus® inhaler, initiating an audio recording, this is classed as an attempt to take the inhaled medication. The pattern of attempts over a defined period will provide an ‘attempted’ rate of adherence. Analysis of the associated acoustic recordings allows for detection of correct inhaler technique, which we take to indicate that the participant actually received the dose they attempted to take. Thus, the pattern of attempted doses with correct technique yields the ‘actual’ rate of adherence.

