The participants will receive a salmeterol/fluticasone Diskus® inhaler with an INCA® device attached for use twice per day as prescribed. This inhaler will be provided free of charge to all participants, regardless of their health pay status, with the relevant professional service being paid by the patient in the usual manner. For all participants, the INCA® device is used to capture data on adherence and inhaler technique. Participants in the intervention and comparator groups will be asked to record their peak expiratory flow with the eMini-Wright® electronic monitor twice daily. In the intervention and comparator groups participants are also provided with a paper-based diary for recording daily symptoms, medication usage and health care utilisation. This diary, based on the Asthma Society of Ireland’s peak flow diary [21], has been developed specifically for this study and piloted in a sample of seven patients. An extract of the diary is provided in Fig. 2 (see Additional file 1).

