**Fig. 2 Fig2:**
[figure not shown]
Extract of participant respiratory diary

After the initial visit (visit 1), follow-up visits are scheduled 30 (visit 2), 60 (visit 3), 150 (visit 4) and 180 (visit 5) days later. At visits 2, 3 and 5 the participants return their inhalers with the INCA® devices. Visit 4 is a dispensing visit. At each of these visits, for control group participants, changes in medications (including new medications) are recorded as is progress towards the participant’s ‘breathing-related goal’. For intervention and comparator group participants this information is also noted along with the SGRQ responses. Assessment of inhaler technique, using an inhaler technique checklist and inhaler technique training based on assessment observations, is given to both intervention and comparator participants.

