### Sample size calculation

Studies in the pharmacy setting have identified rates of baseline rates of attempted adherence amongst asthma patients of below 0.6 [12]. In the primary care setting poor inhaler technique amongst patients with respiratory disease has been identified in preliminary studies conducted using the INCA® device (47 %, standard deviation 33.0). A pre-intervention actual adherence rate of 0.5 at the end of the first month is, therefore, assumed. The primary endpoint is the rate of actual adherence at the end of the study period. A comparison between adherence rates in the intervention and comparator groups will be conducted at the end of months 1, 2 and 6. The sample size is thus dictated by comparisons to be made between these two groups.

It is hypothesised that the intervention group will get closer to the commonly reported level of ‘good’ adherence (≥0.8) [23] improving by 0.2. Adherence in the comparator group may improve as a result of the educational intervention received and an assumed improvement of 0.05 in this group over the study period has been incorporated into the sample size calculation. An intra-class correlation coefficient of 0.025 and a loss to follow-up of 10 % (as observed in a recent similar study conducted in the pharmacy setting [14]) are assumed. With a power of 0.85 at the 0.05 significance level to detect a 0.2 difference in actual adherence between the two groups, a sample size of 75 participants across 25 clusters in each of the intervention and comparator groups is required.

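### The outcome called progressing to good technique tests only the follow-up level, so participants already at 80% in month 1 count as progressing, and its stated model has no baseline technique term

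*Protocol article*

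**What the plan says.** Under the heading on secondary outcomes, the protocol article lists "the number progressing to good technique" and defines good technique in parentheses as at least 80% of all "doses attempted by the patient classified as correct technique". The result is to be compared "at both 2 and 6 months will be assessed". The Statistical methods section repeats the definition, there as a proportion. It assigns a random-effects logistic regression with the individual as the unit of analysis and pharmacy as the random effect. The preceding paragraph of that section says that the multilevel model for the primary outcome controls for both clustering and baseline differences; the paragraph on this endpoint mentions clustering only.

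A pre-intervention measurement exists. The Study design section says that the device records adherence and technique for all participants, and that "follow-up visits are scheduled 30 (visit 2), 60 (visit 3), 150 (visit 4) and 180 (visit 5) days later", with devices returned at visits 2, 3 and 5. Feedback starts at visit 2, and technique assessment and training are described for the follow-up visits. The sample size section treats the first month as pre-intervention. Days 0 to 30 therefore give a technique score in every arm.

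**The concern.** The label describes a change and the rule describes a state. A participant with 85% correct in month 1 and 82% in month 6 satisfies the rule, although technique has slipped slightly. A reader of the results would take the reported proportion as the share who moved from poor to good technique, when it also includes those who were good throughout.

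The between-arm comparison is affected as well. If a large, stable fraction of participants starts above the cut, any difference between arms in that fraction passes almost directly into the endpoint. The stated model has nothing to absorb it. Chance imbalance costs precision. Systematic imbalance would bias the comparison, and the Discussion concedes a risk of selection bias because allocation cannot be concealed from those who recruit.

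**Working it through.** The article states no expected rate or power for this endpoint, so there is no figure of the plan's to reproduce. The check asks what the rule would report if nobody's technique changed.

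**Inputs**
- Cut: at least 80% of attempted doses correct (secondary outcomes section).
- Doses per 30-day window: inhaler supplied "for use twice per day as prescribed", so 2 × 30 = 60 if every dose is attempted. At attempted adherence of 0.6, the upper limit of the baseline figure cited in the sample size section, 0.6 × 60 = 36.
- Spread of technique: "47 %, standard deviation 33.0" (sample size section). The text does not make clear whether 47% is the poor or the correct share, so the mean correct rate is taken as 0.53 and as 0.47.
- Assumptions, not in the article: true individual rates follow a beta distribution, doses are independent given that rate, and each person's rate is the same in both windows.

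**Formula.** For mean m and SD s, t = m(1 − m)/s² − 1, a = mt, b = (1 − m)t. With m = 0.53 and s = 0.33: t = 0.2491/0.1089 − 1 = 1.287, a = 0.682, b = 0.605. With m = 0.47, a and b swap. The number correct in k attempts is then beta-binomial. The pass mark is 48 of 60, or 29 of 36. The joint chance of passing in both windows comes from two binomial counts sharing one true rate.

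**Result with no change in technique**

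| Mean correct rate | Attempts | Good in month 1 | Good at follow-up | Of those good at follow-up, already good in month 1 |
|---|---|---|---|---|
| 0.53 | 60 | 30.4% | 30.4% | 91% |
| 0.53 | 36 | 30.6% | 30.6% | 89% |
| 0.47 | 60 | 24.2% | 24.2% | 90% |
| 0.47 | 36 | 24.4% | 24.4% | 87% |

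The rule would report 24% to 31% as progressing. In the first row, only 30.4% × (1 − 0.912) = 2.7% of all participants actually cross the cut, and they do so by sampling variation.

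**How far baseline imbalance carries through** (first row). The chance of passing at follow-up is 0.912 for those good in month 1. For the others it is 0.304 × (1 − 0.912)/(1 − 0.304) = 0.038 to 0.039, depending on rounding. The difference is about 0.87, so a 10-point imbalance in month-1 status becomes about 8.7 points at follow-up without any treatment effect.

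**How large chance imbalance could be.** With 75 per arm and 30% good in month 1, ignoring clustering: 1.96 × √(2 × 0.3 × 0.7/75) = 1.96 × 0.0748 = 0.147. The 95% range is about ±15 points.

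**Size of the restricted set.** 75 × (1 − 0.304) = 52 to 75 × (1 − 0.242) = 57 per arm. After the assumed 10% loss: 67.5 × 0.696 = 47 to 67.5 × 0.758 = 51.

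**The case against.** The best defence is that the operational rule is clear and identical in all arms, so counting participants who were already good blurs the label but does not by itself favour either arm. That is correct. Under randomisation the cost is precision and interpretability; bias needs a baseline imbalance, which recruitment after known allocation makes possible but which the article does not show. It is also fair to say that covariates for a secondary model are often left to the analysis plan, which is promised and not shown, and that plan may add one. The mismatch between label and definition does not depend on that: both are fixed in the article, in two sections.

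A reader might go further and infer that dividing by attempted doses lets rare users pass by chance, or penalises an arm that uses its inhaler more. The documents do not support either as a material problem. Any opening counts as an attempt ("this is classed as an attempt to take the inhaled medication"), and correctness given an attempt is a legitimate measure of technique. Non-use is captured by the primary outcome, by the companion outcome of good actual adherence and by the attempted rates. Chance passing does occur with very few attempts: at a true rate of 0.6 it is 0.337 with 5 attempts. At 30 attempts it is 0.017, and nothing in the article suggests that near-non-users are common. More use lowers the pass rate only for true rates below the cut. At a true rate of 0.9, passing rises from 0.930 with 10 attempts to 0.994 with 60. Across the assumed spread (mean 0.53), simulated arm-level pass rates are 30.6%, 29.5% and 30.5% at 36, 48 and 60 attempts, a difference of about 1 point. Rules for zero or very few attempts belong in the analysis plan.

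**Conclusion.** The point holds for the label and for the missing baseline term. As defined, the outcome measures having good technique at follow-up, not progressing to it. Under the article's only technique figure and no true change, roughly a quarter to three tenths of participants would be reported as progressing, and about nine in ten of them would have been good already. These sizes rest on the assumed beta shape, on independent doses and on reading the 47% either way; the definitional mismatch needs none of these assumptions. The stated model leaves baseline technique uncontrolled although it is recorded in every arm. That costs precision, and it would bias the comparison if recruitment differed between arms. The attempted-dose denominator is not the fault, and no claim is made that heavier or lighter use distorts the comparison. The matter is confined to one secondary outcome.

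**What to change.** Choose one of two definitions and use it in both the secondary outcomes and Statistical methods sections.

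1. Keep progression, and define it among participants below 80% correct technique in the month-1 recording, with success as at least 80% at 2 and at 6 months. A few percent of this set would cross the cut by chance (about 4% in the first row above), which the between-arm comparison allows for.
2. Rename the outcome as achieving good technique and keep all participants.

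For any analysis of all participants, add month-1 technique to the random-effects logistic model, preferably as the continuous percentage correct rather than as above or below 80%.

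Neither option needs new data or an extra visit. The first reduces the denominator to about 47 to 51 per arm after losses under the assumptions above. The second keeps the full sample and costs one covariate.

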### Sample size calculation

Studies in the pharmacy setting have identified rates of baseline rates of attempted adherence amongst asthma patients of below 0.6 [12]. In the primary care setting poor inhaler technique amongst patients with respiratory disease has been identified in preliminary studies conducted using the INCA® device (47 %, standard deviation 33.0). A pre-intervention actual adherence rate of 0.5 at the end of the first month is, therefore, assumed. The primary endpoint is the rate of actual adherence at the end of the study period. A comparison between adherence rates in the intervention and comparator groups will be conducted at the end of months 1, 2 and 6. The sample size is thus dictated by comparisons to be made between these two groups.

It is hypothesised that the intervention group will get closer to the commonly reported level of ‘good’ adherence (≥0.8) [23] improving by 0.2. Adherence in the comparator group may improve as a result of the educational intervention received and an assumed improvement of 0.05 in this group over the study period has been incorporated into the sample size calculation. An intra-class correlation coefficient of 0.025 and a loss to follow-up of 10 % (as observed in a recent similar study conducted in the pharmacy setting [14]) are assumed. With a power of 0.85 at the 0.05 significance level to detect a 0.2 difference in actual adherence between the two groups, a sample size of 75 participants across 25 clusters in each of the intervention and comparator groups is required.

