**Methods/design:**

The study is a prospective, cluster randomised, parallel-group, multi-site study conducted over 6 months. The study is designed to compare current best practice in care (i.e. routine inhaler technique training) with the use of the INCA® device for respiratory patients in a community pharmacy setting. Pharmacies are the unit of randomisation and on enrolment to the study they will be allocated by the lead researcher to one of the three study groups (intervention, comparator or control groups) using a computer-generated list of random numbers. Given the nature of the intervention neither pharmacists nor participants can be blinded. The intervention group will receive feedback from the acoustic recording device on inhaler technique and adherence three times over a 6-month period along with inhaler technique training at each of these times. The comparator group will also receive training in inhaler use three times over the 6-month study period but no feedback on their habitual performance. The control group will receive usual care (i.e. the safe supply of medicines and advice on their use). The primary outcome is the rate of participant adherence to their inhaled medication, defined as the proportion of correctly taken doses of medication at the correct time relative to the prescribed interval. Secondary outcomes include exacerbation rates and quality of life measures. Differences in the timing and technique of inhaler use as altered by the interventions will also be assessed. Data will be analysed on an intention-to-treat and a per-protocol basis. Sample size has been calculated with reference to comparisons to be made between the intervention and comparator clusters and indicates 75 participants per cluster. With an estimated 10 % loss to follow-up we will be able to show a 20 % difference between the population means of the intervention and comparator groups with a power of 0.8. The Type I error probability associated with the test of the null hypothesis is 0.05.

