### Statistical methods

Statistical analysis will be conducted using IBM SPSS Statistics for Windows, Version 21.0. (Armonk, NY, USA: IBM Corp). Descriptive statistics will be used to evaluate differences in demographic characteristics, clinical condition, medication profile, exacerbation history and quality of life scores between study groups. Categorical variables will be expressed as frequencies or percentages and quantitative variables as means and standard deviations or medians and interquartile ranges.

The primary analysis will be carried out using multilevel modelling (such as mixed linear effects modelling) with the individual as the unit of analysis and controlling for the effects of clustering and baseline differences. An intention-to-treat analysis will be conducted. A secondary, per-protocol analysis will also be conducted. This form of analysis includes only those participants who completed the treatment protocol originally allocated, providing results on the efficacy of the trial.

The proportion of patients achieving good actual adherence (≥80 %) and the proportion progressing to good technique (≥80 % of all doses attempted by the patient classified as correct technique) will be analysed using a random-effects logistic regression with the individual as the unit of analysis and the pharmacy included as the random effect, to control for the effects of clustering.

Changes in patterns of adherence will also be investigated. PEFR, rescue medication use and reported symptoms will be described and used as an indicator of the number of exacerbations per patient which will, in turn, be compared between the groups. Additionally, differences in the SGRQ responses will be examined. For all analyses stratification of patients by diagnosis will be attempted but consideration will be given to the ability to make inferences based on patient numbers.

A full statistical analysis plan will be written by an independent statistical team prior to any analysis being undertaken. Data will be reported in line with the Consolidated Standards of Reporting Trials (CONSORT) 2010 Statement [25] as well as its extension to cluster randomised trials [26] and non-pharmacological treatment [27].

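### Month-1 adherence is a pre-intervention baseline, but the plan lists it as a between-group comparison time and does not secure it as a covariate

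*Protocol article*

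**What the plan says.** Three parts of the protocol article bear on this point.

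- **Status of month 1.** The Sample size calculation section states: "A pre-intervention actual adherence rate of 0.5 at the end of the first month is, therefore, assumed". The Interventions section dates the first device feedback to day 30. Randomisation and allocation refers to a lead-in period meant to deal with a Hawthorne effect. Study design has the device recording adherence in all participants, with devices returned at visit 2 (day 30).
- **Comparison times.** The Sample size calculation section also states: "A comparison between adherence rates in the intervention and comparator groups will be conducted at the end of months 1, 2 and 6". It names the end of the study as the time of the primary endpoint. The Primary outcome section gives comparisons at 2 and 6 months, and the secondary outcomes section uses the same two times for good adherence and good technique.
- **Models.** Under Statistical methods, the primary multilevel model is described as "controlling for the effects of clustering and baseline differences", with no covariate named. The logistic models for good adherence and good technique are described with "the pharmacy included as the random effect, to control for the effects of clustering", and no baseline term is mentioned. A full statistical analysis plan (SAP) is announced; it is not available here.

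**The concern.** A measure taken before the intervention starts should serve as a baseline. Listing it beside months 2 and 6 as a comparison between arms blurs that role. A difference at month 1 says something about recruitment or chance and nothing about feedback that has not yet been given.

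The adjustment wording leaves room for two readings. One is that the baseline value of the outcome always enters the model. The other is that only variables found to differ between arms are adjusted for. The second is data-dependent and does not reliably deliver either precision or protection from imbalance. The logistic models, as stated, have no baseline adjustment at all, although one of their outcomes is progression to good technique, which presupposes a starting level.

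Imbalance is foreseeable here. Pharmacies are allocated on enrolment, pharmacists and participants are unblinded, and the pharmacists then screen and recruit. The Discussion itself acknowledges the resulting risk of selection bias. Month-1 adherence is the most direct variable available for correcting imbalance in the outcome.

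**Working it through.** **Inputs.** From the Sample size calculation section: 75 participants over 25 clusters per arm (3 per cluster), intraclass correlation 0.025, loss to follow-up 10%, month-1 rate 0.5 in both arms, intervention arm "improving by 0.2", comparator arm improving by 0.05. The only standard deviation (SD) given is 33.0 percentage points, reported for inhaler technique; 0.33 is used here as a stand-in for actual adherence. Alpha is 0.05 (Abstract: "The Type I error probability associated with the test of the null hypothesis is 0.05"), taken as two-sided because sidedness is not stated. The correlation r between month-1 and month-6 adherence is not given; 0.3 to 0.7 is assumed.

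**The two differences.** The stated target is 0.2. The assumed improvements imply (0.5 + 0.20) − (0.5 + 0.05) = 0.15.

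**The plan's own figure.** Design effect = 1 + (3 − 1) × 0.025 = 1.05. The number per arm is n = 2(1.960 + z_power)² × 0.33² / difference², rounded up, then multiplied by 1.05 and divided by 0.9. The Methods state: "With a power of 0.85 at the 0.05 significance level to detect a 0.2 difference in actual adherence between the two groups". The Abstract instead gives "population means of the intervention and comparator groups with a power of 0.8".

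| Difference | Power 0.85 | Power 0.80 |
|---|---|---|
| 0.20 | 49 × 1.05 / 0.9 → 58 | 43 × 1.05 / 0.9 → 51 |
| 0.15 | 87 × 1.05 / 0.9 → 102 | 76 × 1.05 / 0.9 → 89 |

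The stated 75 per arm is not reproduced from the full set of inputs. Only partial variants come close: 76 (0.15, power 0.80, two-sided, no inflation) and 74 (0.15, power 0.85, one-sided, design effect but no loss).

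**Power with 75 enrolled per arm.** Effective number per arm = 75 × 0.9 / 1.05 = 67.5 / 1.05 = 64.3. Unadjusted standard error = 0.33 × √(2/64.3) = 0.0582.

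- Difference 0.20: Φ(0.20/0.0582 − 1.96) = Φ(1.48) = 93.0%.
- Difference 0.15: Φ(0.15/0.0582 − 1.96) = Φ(0.62) = 73.1%.

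**With month-1 adherence as covariate.** Residual SD = 0.33 × √(1 − r²), with the design effect held at 1.05.

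| r (assumed) | Power at 0.15 | Power at 0.20 | N per arm for 85% at 0.15 |
|---|---|---|---|
| 0 | 73.1% | 93.0% | 102 |
| 0.3 | 77.1% | 95.0% | 94 |
| 0.5 | 84.5% | 97.8% | 77 |
| 0.7 | 95.0% | 99.8% | 53 |

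At a difference of 0.15, r must be about 0.39 to reach 80% power and about 0.51 to reach 85%. Using a t reference with 48 degrees of freedom (50 clusters less 2) lowers these powers slightly, for example to 71.4% at r = 0 and 83.0% at r = 0.5.

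**Comparison times side by side.** Sample size calculation: months 1, 2 and 6. Primary outcome: months 2 and 6. Secondary outcomes: months 2 and 6. Only the first list includes the month that the same section calls pre-intervention.

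**The case against.** The strongest reply is that adjustment is already planned. The primary model controls for baseline differences, an independent team is to write the SAP before any analysis, and naming covariates is ordinary SAP content. That stands against any claim that the plan gives up the precision available: a reader might infer this, but nothing in the article rules the adjustment out. It also weakens the inference that covariates will be chosen by observed imbalance. The sentence on describing group differences does not mention adherence and is not linked to covariate selection.

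A reader might also infer that month 1 is tested as an outcome. The article says only that a comparison will be made. It assigns month 1 no alpha and no primary or secondary status, and it places the primary endpoint at the end of the study. Describing lead-in adherence by arm is useful in this design, because it would show recruitment imbalance.

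Two factual cautions also stand. The lead-in follows allocation in unblinded, arm-specifically trained pharmacies, and the day-30 start of comparator training is inferred from the Abstract and the visit schedule, since the comparator section gives no dates. In addition, month-1 data depend on the device being returned at visit 2, so early dropouts may have none.

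What remains is the mismatch between the lists of comparison times, adjustment wording that does not secure the most informative covariate, and logistic models stated without it.

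**Conclusion.** The point holds as an improvement that needs no new data. It does not show an error that invalidates the analysis. By the plan's own account month 1 is a pre-intervention measure, and the list of comparison times that includes it conflicts with the Primary outcome section. The main benefit of fixing the covariate is protection against imbalance from unblinded recruitment after allocation, and this does not depend on the power figures.

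The precision benefit is conditional. At the implied 0.15 difference, power rises from about 73% to between 77% and 95% for assumed correlations of 0.3 to 0.7. At the stated 0.2 difference, power is about 93% without adjustment, so the documents do not support saying that the trial needs the covariate to be adequately powered. All these figures rest on an SD reported for technique, a two-sided 0.05 test and correlations that the article does not give.

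**What to change.** 1. In Statistical methods, name continuous month-1 actual adherence as a prespecified covariate in the primary mixed model, included whatever imbalance is observed.
2. Add the month-1 adherence rate to the logistic model for good adherence, and the month-1 technique rate to the model for good technique, keeping the pharmacy random effect in both.
3. Report month 1 by arm descriptively, as baseline, with no test of effect.
4. Reconcile the comparison times in the Sample size calculation and Primary outcome sections.
5. State a simple rule for participants without month-1 data, such as imputing the baseline mean, so that they stay in the intention-to-treat set.

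The cost is a few sentences in the protocol, carried into the SAP. The month-1 recordings are already part of the planned data collection.

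### The sample size paragraph implies a 0.15 difference between arms but states its power for 0.2, and the stated power is 0.85 in one place and 0.8 in another

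*Protocol article*

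**What the plan says.** All the inputs stand in the Sample size calculation section of the protocol article.

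- Starting level: "A pre-intervention actual adherence rate of 0.5 at the end of the first month is, therefore, assumed".
- Intervention arm: a hypothesised improvement of 0.2.
- Comparator arm: "an assumed improvement of 0.05 in this group over the study period has been incorporated into the sample size calculation".
- Other inputs: intra-class correlation 0.025 and 10% loss to follow-up.
- Power statement: "With a power of 0.85 at the 0.05 significance level to detect a 0.2 difference in actual adherence between the two groups".
- Result: "a sample size of 75 participants across 25 clusters in each of the intervention and comparator groups is required".

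The only standard deviation printed is 33.0. It accompanies a 47% figure for poor inhaler technique from preliminary work with the device.

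The Abstract (Methods/design) also gives 75, 10% loss and a 20% difference, but describes a "difference between the population means of the intervention and comparator groups with a power of 0.8". It says 75 per cluster; I read that as per arm, in line with the Methods. The Primary outcome section again uses 20% as the margin the intervention group should reach over the comparator group.

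**The concern.** If the comparator gain is part of the calculation, the difference between arms is 0.15. If the difference is 0.2, either the comparator gain was left out or the intervention arm must rise by 0.25, which the text does not say. The paragraph therefore attaches its power to a difference that its own assumptions do not produce.

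This is the primary comparison, and the sample size is said to be dictated by it. A reader faced with a null result needs to know how likely the trial was to find the effect the planners expected. As printed, that reader would take the miss rate to be 15% (or 20%, from the Abstract) at the expected effect, when those rates are attached to a larger one.

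**Working it through.** **1. Implied difference.** Intervention: 0.50 + 0.20 = 0.70. Comparator: 0.50 + 0.05 = 0.55. Difference: 0.70 − 0.55 = 0.15, against a stated 0.2.

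**2. A check that needs no SD, ICC or loss figure.** If 75 per arm gives 85% power for 0.20 at two-sided 0.05, then 0.20/SE = 1.960 + 1.036 = 2.996. At 0.15 the ratio is 0.75 × 2.996 = 2.247, and power = Φ(2.247 − 1.960) = Φ(0.287), about 61%. One-sided: 0.75 × (1.645 + 1.036) = 2.011, and Φ(2.011 − 1.645) = Φ(0.366), about 64%.

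**3. Trying to reproduce 75 per arm.** Inputs from the section: ICC 0.025; 75/25 = 3 participants per pharmacy, so the design effect is 1 + 2 × 0.025 = 1.05; loss 10%; alpha 0.05. Assumptions: SD 0.33 applies to actual adherence, the test is two-sided, and there is no adjustment for baseline.

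n per arm = 2 × (1.960 + z)² × 0.33² / δ² × 1.05 / 0.90

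| Difference δ | 85% power | 80% power |
|---|---|---|
| 0.20 | 57.0 | 49.9 |
| 0.15 | 101.4 | 88.6 |

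None of these is 75. To obtain 85% at 0.20 with 75 enrolled, the SD would have to be about 0.38 (about 0.40 if all 75 are evaluable). The nearest match found uses a difference of 0.15, a one-sided test, the design effect and no allowance for loss: n is about 74. That needs an unstated one-sided test and drops the stated 10% loss.

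**4. Power with 75 per arm, same assumptions.** After loss: 75 × 0.90 = 67.5; effective n = 67.5/1.05 = 64.3; SE = 0.33 × √(2/64.3) = 0.0582.

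- At 0.15: 0.15/0.0582 = 2.577; Φ(2.577 − 1.960) = 0.731.
- At 0.20: Φ(3.436 − 1.960) = 0.930.
- Detectable difference: 2.802 × 0.0582 = 0.163 at 80% power; 2.996 × 0.0582 = 0.174 at 85%.

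**5. How far the power at 0.15 moves.**

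| Change from step 4 | Power at 0.15 |
|---|---|
| None (SD 0.33, two-sided, after loss) | 73% |
| t reference on 48 df (50 pharmacies − 2) | 71–72% |
| All 75 evaluable | 78% |
| SD 0.28 | 86% |
| SD 0.30 | 81% |
| SD 0.36 | 66% |
| One-sided, after loss | 82% |
| One-sided, all 75 evaluable | 86% |

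**The case against.** The strongest reply is that 0.2 is the design target. The Abstract, the Primary outcome section and the power sentence all use it, and a trial may properly be powered for a target difference rather than the expected one. On this view the fault lies in loose wording about the intervention arm's gain, or about how the comparator's 0.05 entered. That is possible, but the paragraph would still need rewording, because as printed the arm-level assumptions and the between-arm difference disagree.

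A reader might go further and infer that the trial has 73% power rather than 85%. The documents do not support that.

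- The SD of 33.0 describes inhaler technique. Actual adherence also depends on missed and mistimed doses, so its SD may differ. The mismatch in step 3 itself suggests that the planners may have used another value.
- Sidedness is not stated. One-sided, at SD 0.33 with all 75 evaluable, power at 0.15 is about 86%.
- The Methods do not say whether 75 is before or after the 10% loss, although the Abstract's wording suggests before.
- The Statistical methods section plans a multilevel model that controls for baseline differences. With variance multiplied by 1 − r², an assumed correlation of 0.4 between month-1 and final adherence lifts 73% to about 80%, and 0.51 lifts it to about 85%. The article gives no such correlation.

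These points stand. They limit what can be said about the size of any shortfall. They do not remove the contradiction, which needs none of these inputs.

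**Conclusion.** The paragraph is wrong as written. Its arm-level assumptions give 0.15, its power statement uses 0.2, and the article gives both 0.85 and 0.8 as the power. The one SD-free consequence is that 85% at 0.20, two-sided, means about 61% at 0.15. If instead the 85% belongs to 0.15, the printed 0.2 is the error.

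The 73% at 0.15 and 93% at 0.20 hold only for SD 0.33, ICC 0.025, three per pharmacy, two-sided 0.05, 10% loss from 75 and an unadjusted comparison. They show the scale of the ambiguity. They do not establish that the trial is underpowered, since the article does not fix the inputs that would decide it.

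**What to change.** Rewrite the Sample size calculation paragraph to state:

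1. one between-arm difference that agrees with the assumed gain in each arm;
2. the SD of actual adherence actually used, and its source;
3. whether the test is one- or two-sided;
4. whether 75 per arm is before or after the 10% loss;
5. one power value, recomputed from these inputs.

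If 0.2 is kept as the target, give the power at 0.15 beside it, or give the detectable difference. With SD 0.33, two-sided and after loss, that is about 0.16 at 80% power and 0.17 at 85%. If credit is taken for baseline adjustment, print the assumed correlation. Then bring the Abstract and the Primary outcome section into line on the difference, and the Abstract on the power.

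The cost is one corrected paragraph and matching edits in two other places. The stated power may become less favourable. Enrolment, endpoint and analysis do not change.
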